#### Control intervention

The control treatment is a computer-based training for rapid eye movements and is part of a comprehensive cognitive rehabilitation/brain performance training software suite (RehaCom, Hasomed GmbH, Magdeburg, Germany) [24]. The patient is asked fixate a central target and to respond to peripheral stimuli moving towards the center of the visual field. As in the VRT arm, a chin support is provided. Some guidance is given, for example a horizontal line that facilitates the differentiation between the fixation target and the moving object. The program has ascending levels of difficulty depending on the size, the contrast, and the velocity of the moving object. As in the VRT arm, patients are instructed to exercise for 30 minutes each day, for 6 months in total. The control treatment enables the patient to compensate loss of visual function by the use of saccadic eye movements [25] rather than inducing a true recovery of visual dysfunction.

### Outcome parameters

The primary outcome parameter is the extend of the visual field after 3 and 6 months of training as determined by both HRP (see above) and threshold 30 degree automated perimetry (HFA 720, Zeiss Meditec AG, Germany). The secondary outcome parameters are outlined below and will be evaluated as displayed in Table 1. Visual acuity measurements are made using the Freiburg Visual Acuity and Contrast Test (FRACT): Landolt rings (ISO 8596) with a constant high contrast and decreasing size are presented at 4 m distance on a computer screen, and the patient is asked to report the perceived direction of the opening of each Landolt ring presented [26]. Contrast sensitivity is measured using FRACT with Landolt rings of equal size but decreasing contrast. Measurements of glare contrast sensitivity are made using the FRACT program as described above and a purpose built glare source (Beuth University of Applied Sciences, Berlin, Germany). The glare source consists of a white frame with eight white LEDs (approximately 8,500 LUX each) circularly arranged around the TFT-screen used for FRACT testing. Recording of VEP allows the conductance velocity and the amplitude of the visual signal evoked by stimulating the retina to be measured. In ON, both a delay of latency and lowered amplitude of this signal is typical. Spectral domain optical coherence tomography (OCT; Spectralis, Heidelberg Engineering, Germany; software version 5.1) is used to measure the retinal nerve fiber layer thickness (RNFLT) of the retina circularly around the optic nerve head and the volume of the macula, as both parameters are increasingly recognized as markers for neuroaxonal degeneration in MS [27]. Color perception is tested using pseudo-iso-chromatic plates (Ishihara, 14-plate version) and a Multi Color Anomaloscope (HMC, Oculus GmbH, Wetzlar, Germany), whereby the Ishihara test serves as a screening-test which is followed by an anomaloscope measurement in case of any abnormality [28]. The quality of stereoscopic vision is assessed using the stereo fly test (Titmus test). The patient wears polarized glasses and views a polarized fly. In normal stereoscopic vision a three-dimensional image of the fly is perceived. The cover/uncover test is performed to detect any strabismus or heterophoria. The International Reading Speed Texts (IReST) are used to measure the reading ability [29]. The Trail Making Test (TMT) is a popular neuropsychological test that provides information on visual search, scanning, speed of processing, mental flexibility, and executive functions. The patient is asked to connect 25 randomly spread numbers on a sheet of paper, and the time required for this task is measured [30]. The Tests of Attentional Performance (TAP 1.7) measure alertness via reaction time and provide a global measure of processing speed of the brain [31]. Alertness is defined as a state of general wakefulness in which a person can quickly react to concrete requirements. The questionnaires that are used to evaluate the health-related quality of life (HRQL) with regard to vision are the National Eye Institute Visual Functioning Questionnaire (NEI-VFQ 39) [32], the Impact of Visual Impairment Scale (IVIS) (which is the visual subscale of the Multiple Sclerosis Questionnaire of Life Inventory (MSQLI)) and a Visual Analogue Scale (VAS). The Short Form 36 (SF-36) is a generic measurement of the HRQL [33,34], the Health 49 is a freely available questionnaire (http://www.hamburger-module.de) [35] and the Fatigue Severity Scale (FSS) is a self-rating, nine-item questionnaire which measures the severity of fatigue [36] which has been validated in a large sample of MS patients [37]. The Beck Depression Inventory (BDI) is used mainly to control for depression as a possible confounder [38]. Finally, the following demographic data will be collected: disease course (clinically isolated syndrome or relapsing-remitting MS or secondary-progressive MS [39], date of first manifestation, date of first diagnosis, side of ON, current treatment, expanded disability status scale [40]), and vital parameters (blood pressure, heart rate, weight, body height, age, and ethnicity).

**Table 1 T1:** Visits and measurements

**Measurements**	**Visit 0 (baseline visit)**	**Visit 1 (after 3 months)**	**Visit 2 (after 6 months)**
Neurostatus	X		
Visual field	X	X	X
Contrast sensitivity	X	X	X
Glare sensitivity	X	X	X
Visual acuity	X	X	X
Visual evoked potentials	X	X	X
Optical coherence tomography	X	X	X
Color perception	X	X	X
Binocular vision	X	X	X
Eye movement/	X	X	X
Leading eye reading speed	X	X	X
Trial making test	X	X	X
Alertness	X	X	X
Health related quality of life	X	X	X

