**Methods/design:**

A randomized, controlled, patient- and observer-blinded clinical pilot study (VISION study) was designed to evaluate the efficacy of vision restoration therapy in optic neuritis patients. Eighty patients with a residual visual deficit after optic neuritis (visual acuity ≤0.7 and/or scotoma) will be stratified according to the time of optic neuritis onset (manifestation more than 12 months ago (40 patients, fixed deficit) versus manifestation 2 to 6 months ago (40 patients, recent optic neuritis)), and randomized into vision restoration therapy arm or saccadic training arm (control intervention). Patients will be instructed to complete a computer-based visual training for approximately 30 minutes each day for a period of 6 months. Patients and evaluators remain blinded to the treatment allocation throughout the study. All endpoints will be analyzed and *P*-values < 0.05 will be considered statistically significant. The primary outcome parameter will be the expansion of the visual field after 3 and 6 months of treatment as determined by static visual field perimetry and high resolution perimetry. Secondary outcome variables will include visual acuity at both low and high contrast, glare contrast sensitivity, visually evoked potentials, optical coherence tomography and other functional tests of the visual system, alertness, health-related quality of life, fatigue, and depression.

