## Methods/design

### Design and setting

The VISION study is a monocentric, randomized, controlled, and double-blind clinical trial conducted at the NeuroCure Clinical Research Center at the Charité - Universitaetsmedizin, Berlin, Germany. Recruitment started in 2011. Eighty patients with a diagnosis of past or recent ON will be stratified according to the onset of ON. The first group will comprise patients with ON manifestation at least 1 year in the past. The second group will comprise patients with ON onset between 2 and 6 months in the past. These two groups will be randomized 1:1 into the VRT group and the control intervention group, with the latter receiving a saccade training (RehaCom, Hasomed GmbH, Magdeburg, Germany). The detailed study design is provided below according to the revised CONSORT statement [22,23].

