### Statistical analysis

This study is designed as a pilot study because sufficient data that would allow a reasonable *a priori* calculation of sample size are not yet available. All endpoints will be analyzed and described descriptively. The null hypothesis is as follows: VRT has no influence on the visual outcome after ON. Evaluation of endpoints will be carried out by both “intention-to-treat” and “per-protocol” analyses. Statistical tests and presentations will be appropriate to the category and distribution of the respective variables. All tests will be accomplished with a type one error (α = 0.05; bilateral). All calculations will be performed using SPSS, Version 20 (SPSS, Inc., Chicago, IL, USA).

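### The primary outcome is four unranked results (two perimetry methods at two visits), each tested at 0.05, with no rule for what counts as a positive trial

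*Protocol article*

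**What the plan says.** The protocol article speaks of one primary outcome parameter in two places.

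- Outcome parameters: "The primary outcome parameter is the extend of the visual field after 3 and 6 months of training as determined by both HRP", followed by the second method, "threshold 30 degree automated perimetry (HFA 720, Zeiss Meditec AG, Germany".
- Abstract, Methods/design: the same structure, as "expansion of the visual field after 3 and 6 months of treatment as determined by static visual field perimetry and high resolution perimetry".

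The inferential rules are equally broad.

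- Statistical analysis: "All tests will be accomplished with a type one error (α = 0.05; bilateral".
- Abstract: all endpoints are analysed, and P-"values < 0.05 will be considered statistically significant".
- Statistical analysis: "Evaluation of endpoints will be carried out by both" intention-to-treat and per-protocol analyses, with neither named as the main one. The same section gives a single null hypothesis of no influence of VRT on visual outcome, and also says that endpoints will be presented descriptively.

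On the onset groups, Design and setting says: "Eighty patients with a diagnosis of past or recent ON will be stratified according to the onset of ON" and "These two groups will be randomized 1:1 into the VRT group and the control intervention group". The Discussion comments on the size of each group (40 patients, 20 per arm) as a limitation.

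Two further statements bear on the choice of instrument. The Vision restoration therapy section says that the training algorithm is driven by HRP data. The Discussion says that a training effect should be visible by some means other than HRP as well.

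**The concern.** A reader with the final data could not tell from this text whether the primary outcome was met. With two methods at two visits there are four P-values, each with its own 0.05 threshold. One significant result out of four could be reported as a significant primary result. So could four out of four, or agreement of the two methods at one visit, and the text excludes none of these readings.

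This matters most for HRP. VRT directs its stimuli with HRP data, so HRP lies close to the trained task. The Discussion itself asks for an effect beyond HRP, but the primary outcome as written would let an HRP-only result at 3 months stand as a significant primary finding.

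What is at stake is what the pilot can be said to have corroborated. The Discussion gives that as its purpose before larger confirmatory trials.

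**Working it through.** **Inputs from the protocol article**

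- Level: two-sided 0.05 for every test (Statistical analysis).
- Methods: 2, HRP and threshold 30-degree perimetry (Outcome parameters).
- Visits: 2, at 3 and 6 months (Outcome parameters; also the visit table).
- Primary tests, with onset groups pooled and one analysis set: 2 × 2 = 4.

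**Inputs assumed**

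- Correlation between instruments and between visits. The article gives none, so a range is used.
- Power of 80% per test. The article has no sample-size calculation, so this only illustrates the loss under a strict rule.

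**The stated figure.** The 0.05 is a nominal level, not a derived result. Per test, 2 × (1 − Φ(1.96)) = 0.05, so it holds.

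**If any one of the four results counts.** For independent tests the chance of at least one false positive is 1 − (1 − 0.05)^4 = 1 − 0.8145 = 0.185. For correlated tests, the four statistics were simulated as multivariate normal. The correlation between two statistics is the product of the instrument and visit correlations where both differ.

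**If all four must be significant in the same direction.** Two quantities come from the same model. The first is the false-positive chance. The second is the power when each statistic has mean 1.960 + 0.842 = 2.802, which gives 80% power singly.

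| Correlation, instruments / visits | False positive, any of four | False positive, all four | Power, all four |
|---|---|---|---|
| 0 / 0 | 18.5% | <0.1% | 41% (0.8^4) |
| 0.3 / 0.5 | 17% | <0.1% | 51% |
| 0.5 / 0.7 | 15% | 0.2% | 57% |
| 0.7 / 0.8 | 13% | 0.6% | 62% |
| 0.9 / 0.9 | 10% | 1.6% | 69% |

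**If both methods must agree at one named visit.** For instrument correlations from 0 to 0.9, the false-positive chance is 0.1% to 3.0%, so this reading brings no inflation.

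**Size of the gap.** At correlations 0.5/0.7, the choice between the two extreme rules moves the false-positive chance from 0.2% to 15%. The article does not make that choice.

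**The case against.** The case against has several parts.

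- **The 5% is a per-test level.** The article claims no trial-wide error rate. This stands: a reader might infer that a stated 5% has been shown false, but no stated figure is refuted.
- **Onset groups.** A reader might infer that the primary outcome is tested separately in each group, which would make eight tests and a still higher error. The documents do not support that. Onset group is a randomisation stratum, the null hypothesis is global, and the Discussion mentions group sizes only as a limitation. Inflation from strata would arise only if such tests were run.
- **Analysis sets.** Intention-to-treat and per-protocol share most patients and should not be counted as doubling the tests. This stands. What remains is that neither is named as deciding, and by itself that could be left to an analysis plan.
- **Meaning of both.** The wording of the primary outcome, together with the Discussion's demand for more than HRP, could mean that the two methods must agree. That is a fair reading and would remove the inflation. The text does not settle it, and it leaves the two visits unranked.
- **Pilot status.** The trial is declared a pilot, has no go/no-go criterion and leaves confirmation to a larger study. This lowers the stakes, and strict error control over all endpoints would partly be a matter of preference. It does not remove the point, because the abstract still plans to call any P below 0.05 significant.
- **Unseen analysis plan.** Multiplicity detail may sit there. However, the article does not merely leave the primary outcome open: it fixes it as four results under a blanket significance rule, so ranking them would change that text.

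**Conclusion.** The point holds in a limited form. The primary outcome is badly fixed: four unranked results at 0.05 each, with no success rule. If any single result counts, the chance of at least one false-positive primary result is about 10-19%, or two to nearly four times the per-test level. If all four must be positive, it is below 2%, at a substantial cost in power (51-62% instead of an assumed 80%, at correlations 0.3/0.5 to 0.7/0.8).

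These figures assume one analysis set, pooled onset groups, normally distributed test statistics and the stated correlations. They are conditional on the success rule, which the article does not give. Given the pilot aim, this should be fixed, but it does not invalidate the trial.

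**What to change.** Amend the abstract, Outcome parameters and Statistical analysis before unblinding.

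1. Name one primary comparison: visual field by threshold 30-degree automated perimetry at 6 months, VRT against control, all randomised patients by intention-to-treat, two-sided 0.05. Threshold perimetry goes first because the training is built on HRP data and the Discussion asks for an effect beyond HRP. A case for HRP exists, since the article describes it as locating scotoma borders more precisely, but it does not meet that demand.
2. Test HRP at 6 months, then the two 3-month results in a stated order, each at 0.05 and only while the preceding step is significant. Alternatively, report these three as supportive. If all four are to stay co-primary with any one sufficient, a Bonferroni level of 0.05/4 = 0.0125 each keeps the overall error at or below 5%.
3. Describe per-protocol and onset-group results as supportive.
4. Replace the blanket significance sentence in the abstract by a statement that P-values for all other endpoints are exploratory, and align the descriptive wording in Statistical analysis with it.

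The cost is a wording amendment with no change to visits, measurements or sample size. The one loss is that an isolated HRP or 3-month result can no longer be called a positive primary result. At the time of the article 16 patients had been randomised and six had completed treatment, so the change could still have been made early.

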Against this background, we introduce the protocol for a randomized, controlled clinical pilot study evaluating the efficacy of VRT in patients with incomplete visual recovery upon ON. We hypothesize that VRT is superior to saccadic training which is used here as a control intervention, with respect to i) restitution of residual visual field defects; ii) additional parameters of both visual function and integrity of the visual system including low contrast and color vision, conductivity, and retinal morphology; and iii) improvement in quality of life estimates.

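### The primary outcome is a follow-up level in the Methods and a change from baseline in the Abstract; one definition with baseline adjustment would settle it

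*Protocol article*

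**What the plan says.** The primary outcome is defined twice in the protocol article.

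- Outcome parameters: "the extend of the visual field after 3 and 6 months of training". This is the size of the field at follow-up.
- Abstract, Methods/design: "The primary outcome parameter will be the expansion of the visual field after 3 and 6 months of treatment". This is a gain relative to the starting field.

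Both definitions name the 3- and 6-month visits and two perimetry methods, high-resolution perimetry and static (30-degree threshold) perimetry. Table 1 schedules the visual field at Visit 0 as well as at 3 and 6 months.

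The first hypothesis in the Background concerns "restitution of residual visual field defects", and the Background reports an earlier trial's results as degrees gained or lost. Both point towards change. The null hypothesis in Statistical analysis refers only to visual outcome and fits either reading.

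On method, the Statistical analysis section says: "Statistical tests and presentations will be appropriate to the category and distribution of the respective variables". Testing is two-sided at 0.05. No model and no covariate is named, and none is ruled out.

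**The concern.** A level and a change are different variables. Compared between arms without adjustment, they give different point estimates, standard errors and p-values in the same patients. All endpoints are tested at 0.05, so which variable is tested can decide whether the primary result is called significant. With both definitions in print, the choice could be made after the data are seen.

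The two also respond in opposite directions to a chance difference in starting field between the arms. A level comparison carries part of that difference forward, and a change score over-corrects for it. The strata are small (20 per arm in each), so chance differences of some size are to be expected.

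**Working it through.** **Inputs from the article.** There are 80 patients in two onset strata, randomised 1:1: 80 / 2 / 2 = 20 per arm per stratum, or 40 per arm pooled. This agrees with the Discussion. Alpha is 0.05 two-sided. The article gives no power, effect size or SD, so there is no stated figure to reproduce.

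**Assumptions.** The correlation r between baseline and follow-up field is not given, so a range is shown. SDs at baseline and follow-up are taken as equal, and the relation as linear.

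**Relative variance of the arm difference.** Level = 1. Change = 2(1 − r). Baseline-adjusted (ANCOVA) = 1 − r². The ratio of ANCOVA to change is (1 − r²) / [2(1 − r)] = (1 + r)/2.

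| r | Level | Change | ANCOVA | ANCOVA / level | ANCOVA / change |
|---|---|---|---|---|---|
| 0.3 | 1 | 1.40 | 0.91 | 91% | 65% |
| 0.5 | 1 | 1.00 | 0.75 | 75% | 75% |
| 0.7 | 1 | 0.60 | 0.51 | 51% | 85% |
| 0.9 | 1 | 0.20 | 0.19 | 19% | 95% |

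The better of the two unadjusted versions switches at r = 0.5, so the wording of the endpoint matters.

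**Power for a true difference of 0.5 follow-up SD** (illustrative; normal approximation, standard error √(2/n) × √(variance factor)):

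| r | n per arm | Level | Change | ANCOVA |
|---|---|---|---|---|
| 0.5 | 20 | 35% | 35% | 45% |
| 0.7 | 20 | 35% | 53% | 60% |
| 0.5 | 40 | 61% | 61% | 73% |
| 0.7 | 40 | 61% | 82% | 88% |

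**Chance imbalance.** With 20 per arm the baseline difference has standard error √(2/20) = 0.32 SD, so a gap above 0.3 SD in either direction has probability of about 34%. With 40 per arm it is √(2/40) = 0.22 SD, and the probability is about 18%. At r = 0.7, a gap of 0.3 SD shifts a level comparison by 0.7 × 0.3 = 0.21 SD and a change comparison by (0.7 − 1) × 0.3 = −0.09 SD.

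**Why adjustment removes the conflict.** Let Y₀ and Y₁ be the baseline and follow-up field and T the arm. Suppose change is modelled as Y₁ − Y₀ = a + bT + cY₀. Adding Y₀ to both sides gives Y₁ = a + bT + (c + 1)Y₀. The treatment coefficient b, its standard error and its p-value are unchanged; only the baseline slope differs. The same holds with the onset stratum added, and for a mixed model on both visits. It applies to absolute change in the same unit, not to percentage change.

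**The case against.** The strongest reply is that only the endpoint wording is at fault. The Abstract, the first hypothesis, the earlier results quoted in the Background and the scheduled baseline field all fit change, and one sentence in Outcome parameters is out of line. A condensed article commonly leaves model and covariates to a fuller plan, and this is a pilot that its authors expect to be followed by a larger confirmatory trial.

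Much of this stands. A reader might infer from the sentence on tests that unadjusted two-sample tests are planned and that about half the information will be lost. The article does not support that. The sentence names no test and is compatible with ANCOVA or a mixed model, and the loss of about half arises only for an unadjusted level comparison at an assumed r of 0.7. Against a change score the variance saving at that r is 15%, and at r = 0.9 it is 5%.

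A reader might also take the wide acuity range in Study cohort as proof of very unequal starting fields. Acuity is a different variable, so the range does not show this. A scotoma is required only when acuity exceeds 0.7, so some patients may have little field defect, and a ceiling in the field measure is possible. Nor is either unadjusted version biased on average under randomisation; they differ in precision and in their response to an observed imbalance.

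The conflict itself remains. The sentence out of line is the one in the Methods that defines the endpoint, and supporting text that leans one way does not replace a single definition.

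**Conclusion.** The point holds as a contradiction in the definition of the primary outcome, together with a nearly free improvement that resolves it. The Abstract and the Outcome parameters section must agree.

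Its statistical size is conditional. If the analysis were unadjusted, the adjusted comparison would have 75% to 19% of the variance of a level comparison, and 75% to 95% of that of a change comparison, for r from 0.5 to 0.9. These figures rest on an assumed r, equal SDs and a linear relation, and are large-sample results. If baseline adjustment is already planned elsewhere, nothing is lost and only the wording needs correcting.

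A reader might conclude that 6 months should become the only primary time point. Both definitions name 3 and 6 months, so that is a separate decision and this contradiction does not require it.

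**What to change.** Use one definition in the Abstract and in Outcome parameters. State that, for each perimetry measure, the primary estimate is the between-arm difference in visual field at the 3- and 6-month visits, adjusted for the Visit 0 field and the onset stratum. This can be done by ANCOVA at each visit or by a mixed model on both visits. The mixed model also lets patients who miss the last visit contribute their 3-month value.

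The baseline field is already collected, so no new measurement is needed. The two covariates cost about two degrees of freedom: in a pooled single-visit analysis, 80 − 4 = 76 residual degrees of freedom instead of 80 − 2 = 78. Model assumptions need a check if the field measure has a ceiling, and the fallback should be named in advance. At publication 16 patients had been randomised and six had completed treatment, so the wording could be fixed before most outcome data existed; in any case it should be fixed before the arms are compared.

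### Follow-up anomaloscope readings depend on that visit's Ishihara result, so comparing the available readings between arms would be biased toward no effect

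*Protocol article*

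**What the plan says.** The Background of the protocol article hypothesises that vision restoration therapy (VRT) is superior to saccadic training on, among other things, "additional parameters of both visual function and integrity of the visual system including low contrast and color vision". The Outcome parameters section names two instruments: "Color perception is tested using pseudo-iso-chromatic plates (Ishihara, 14-plate version) and a Multi Color Anomaloscope". It then links them by a rule: "the Ishihara test serves as a screening-test which is followed by an anomaloscope measurement in case of any abnormality". The rule names no visit.

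The timing comes from the same section: "The secondary outcome parameters are outlined below and will be evaluated as displayed in Table 1". In Table 1 the row "Color perception" is marked at visit 0, visit 1 (3 months) and visit 2 (6 months).

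On analysis, the Statistical analysis section says: "Evaluation of endpoints will be carried out by both “intention-to-treat” and “per-protocol” analyses". It does not say which of the two colour tests is compared between arms, or how a patient without an anomaloscope reading is scored.

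**The concern.** Screening first and quantifying only the abnormal cases is a sensible diagnostic sequence. Used again after randomisation to measure an efficacy outcome, it lets one outcome decide whether another is observed. A patient whose Ishihara result becomes normal at 3 or 6 months has no anomaloscope reading at that visit. If VRT improves colour vision, more VRT patients than controls lose their reading in this way, and those who keep it are the more impaired part of each arm. A comparison of the available readings is then no longer a comparison of the randomised groups.

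This is more than an analysis detail that the article could leave to a fuller document. The rule governs which data are collected, and a later analysis plan can choose a score for a normal screen but cannot recover a reading that was never taken. At stake is one secondary measure: a real effect on colour vision could be understated or missed on the quantitative instrument.

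**Working it through.** **Step 1: the passages side by side.** The rule under Outcome parameters makes the anomaloscope conditional on an abnormal Ishihara result. Table 1 repeats colour perception at all three visits, and nothing limits the screen to visit 0. The natural reading is that the two-step procedure runs at each visit. A reading at visit 1 or 2 then depends on a result obtained after randomisation.

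**Step 2: inputs for a size.** The article gives no figure to reproduce: it has no sample-size calculation and no rate of abnormal or normalised colour vision. From the article come 1:1 allocation ("These two groups will be randomized 1:1 into the VRT group and the control intervention group"), 80 patients and so 40 per arm, and two-sided α = 0.05. Everything else is assumed:

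- all 40 patients per arm are Ishihara-abnormal at baseline (a generous assumption for sample size);
- the follow-up anomaloscope deficit x has SD 1, higher being worse, with mean 0 in controls and −d in the VRT arm, d = 0.3, 0.5 or 0.8;
- the Ishihara score s has SD 1 and correlation ρ = 1.0, 0.8 or 0.6 with x; its mean is 0 in controls and −ρd in the VRT arm;
- Ishihara is abnormal if s > c, with c = Φ⁻¹(p), where p = 20, 40 or 60% is the share of controls who are normal at follow-up.

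**Step 3: formula.** With λ(a) = φ(a) / [1 − Φ(a)], the mean deficit among measured patients is ρλ(c) in controls and −d + ρλ(c + ρd) in the VRT arm. The expected difference among measured patients is therefore

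d − ρ[λ(c + ρd) − λ(c)].

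The bracket is positive whenever d > 0 and ρ > 0, so in this model the difference always shrinks.

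**Step 4: numbers.**

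- Middle of the grid (ρ = 0.8, p = 40%, d = 0.5): c = −0.2533, λ(c) = 0.3863/0.6000 = 0.644. For VRT, c + ρd = 0.1467, λ = 0.3947/0.4417 = 0.894. Difference 0.5 − 0.8 × (0.894 − 0.644) = 0.30 SD, or 60% of the true value.
- Severe corner (ρ = 1, p = 60%, d = 0.8): 0.8 − (0.2291/0.1461 − 0.3863/0.4000) = 0.8 − (1.568 − 0.966) = 0.198 SD, or 25%.
- Mild corner (ρ = 0.6, p = 20%, d = 0.3): 0.3 − 0.6 × (0.3205/0.7459 − 0.2800/0.8000) = 0.3 − 0.6 × (0.430 − 0.350) = 0.252 SD, or 84%.

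A simulation with 400,000 patients per arm gives the same values. For a true benefit of 0.5 SD:

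| ρ | Controls normal at follow-up | Difference among measured (SD) | Measured VRT / control, of 40 each | Approximate power |
|---|---|---|---|---|
| 1.0 | 20% | 0.26 | 25 / 32 | 0.27 |
| 1.0 | 40% | 0.18 | 16 / 24 | 0.15 |
| 1.0 | 60% | 0.13 | 9 / 16 | 0.09 |
| 0.8 | 20% | 0.35 | 27 / 32 | 0.36 |
| 0.8 | 40% | 0.30 | 18 / 24 | 0.23 |
| 0.8 | 60% | 0.27 | 10 / 16 | 0.15 |
| 0.6 | 20% | 0.42 | 28 / 32 | 0.42 |
| 0.6 | 40% | 0.39 | 19 / 24 | 0.30 |
| 0.6 | 60% | 0.37 | 12 / 16 | 0.20 |

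With the anomaloscope done in all 40 per arm, power for 0.5 SD is about 0.61.

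**The case against.** The strongest reply is that the article plans no such comparison. The listed outcome is colour perception, not the anomaloscope reading. No sentence confines an arm comparison to measured patients, and intention-to-treat is stated. A patient who normalises has a recorded result, a normal screen, which could be scored as the best category and kept in the analysis. The scoring rule may stand in the full protocol or analysis plan. This stands, and it is why the bias is stated here only for the case that available anomaloscope values are compared. It does not remove the point, because the missing readings follow from the collection rule and neither intention-to-treat nor a scoring rule brings them back.

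Second, the text does not say that the screen is repeated at follow-up, and screening once at baseline is not excluded. That is so. The repeated reading is an inference from Table 1, though the natural one. If a single screen was intended, one sentence settles it.

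Third, a reader might infer that the comparison would be among patients who did not improve, or that colour perception as an outcome is lost. The documents support neither. Measured patients would include those who improved but remain abnormal and any who became abnormal after baseline, and the Ishihara result exists for everyone.

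Fourth, this is one component of one of many secondary measures in a pilot described as preceding confirmatory trials, and an attenuated difference does not by itself produce a false claim of benefit. Both are true and limit the weight of the point.

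**Conclusion.** The concern holds in a conditional form and is minor. On the natural reading of the rule with Table 1, whether a follow-up anomaloscope value exists depends on a post-randomisation result that treatment may change. If available values are compared, the difference is biased toward no effect, with about 25 to 84% of it remaining over the assumed grid. For a true 0.5 SD benefit, 0.13 to 0.42 SD remains, and power falls from about 0.61 to between 0.09 and 0.42.

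These sizes rest on normal scores, a uniform benefit, all patients abnormal at baseline and assumed normalisation rates. The direction holds throughout the grid; the size cannot be fixed from the documents. A reader might be drawn to a single figure such as a 70% loss. That figure needs a 0.5 SD benefit, half of the controls normal at follow-up and perfectly correlated tests (c = 0, ρ = 1: 0.5 − (0.352/0.3085 − 0.798) = 0.157 SD). It lies toward the severe end, and nothing in the article supports those inputs. Half of the planned sample is the long-standing stratum, whose deficit the abstract calls fixed, so normalisation in half of the controls is hard to presume.

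**What to change.** 1. Name the number of Ishihara plates read correctly, in all randomised patients at visits 1 and 2, as the between-arm colour endpoint. The test is already done in everyone, so this adds no testing. It should be confirmed that the plate count is recorded and not only normal or abnormal.
2. Let the visit 0 Ishihara result decide who has the anomaloscope, and measure those patients at visits 1 and 2 whatever Ishihara then shows. The group is then defined by a baseline result, and the arm comparison within it keeps the protection of randomisation. The cost is one sentence in the protocol and some extra testing time on equipment already in place.
3. Treat anomaloscope values from visits already completed under the conditional rule as descriptive only. The Trial status section reports 16 patients randomised, six of them through 6 months, so most of the planned 80 would still be covered by the change.
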